### Attrition and Compliance

We expect to recruit approximately 80% (100/120) of eligible participants—that is, 80% of all youth enrolled in the IACP—to our study, which is a conservative estimate based on previous literature [41]. Participation in the research study entails no additional commitment from eligible participants, given that all study materials are also an integral part of the IACP. Further, we expect attrition to be less than or equal to 25% (25/100), based on the current literature, which suggests a 7% to 42% dropout rate for adolescents enrolled in day treatment programs for the treatment of EDs [17,42-45], and also considering the flexible, modular, and hybrid nature of our program, which may allow us to improve retention rates.

Participants who attend at least one session per week of treatment in the IACP (and complete both pre- and postintervention materials) will be considered sufficiently exposed to the intervention and, thus, will be included in the data analysis on the preliminary effectiveness of the program.

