### Data Collection

Data will be collected at baseline (clinical and demographic information and preintervention self-report questionnaires), weekly (youth and parent satisfaction questionnaires), and immediately after the end of treatment (postintervention self-report and satisfaction questionnaires), as outlined in Figure 1. The clinical program coordinator will be responsible for collecting all data, deidentifying the data, and sending all deidentified data (including only participants’ random study ID) to the research team. Data to be collected include demographic and clinical information at baseline, growth curve charts, BMI pre- and postintervention, self-report standardized outcome questionnaires, acceptability (satisfaction) surveys, and measures of feasibility. All self-report questionnaires and surveys will be completed either on paper (if participants are present on site) or web-based (on a laptop or smartphone) using password-protected interactive PDF format questionnaires that will be sent to the participants using a secure email address.

Demographic and clinical information at baseline, including age, sex, level of education, diagnosis, presenting ED symptoms, duration of illness, ED treatment history (including past hospitalizations), maximum and minimum weight, comorbid symptomatology, and past medical history, will be collected by the clinical program coordinator during the intake visit for the IACP.

BMI will be calculated at baseline and at the end of treatment. Weight (with clothing on but without coats, shoes, boots, or cold weather accessories) and height (without shoes) will be measured during the first and last appointments with the clinical team using an electronic scale and a standard wall measuring scale. BMI will be calculated by dividing body weight in kilograms by the square of the height in meters.

Feasibility data will be collected by the IACP clinical staff throughout the duration of the study and will include recruitment and retention rates, in addition to measures of adherence to the protocol (Table 1).

**Table 1 table1:** Summary of feasibility measures.

Outcome	Target
Recruitment rate	80% (100/120) of eligible participants (ie, of all adolescents participating in the IACP^a^) will enroll in the study and complete the baseline measure.
Retention rate	≤25% (25/100) of enrolled participants lost to follow-up.

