Adherence to protocol	At least 70% (70/100) of participants complete at least one therapeutic session per week of treatment in the IACP. At least 70% (70/100) of participants complete all pre- and postintervention questionnaires. At least 70% (70/100) of participants complete at least one therapeutic session per week and all pre- and postintervention questionnaires.

^a^IACP: Intensive Ambulatory Care Program.

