### Outcome Measures

A set of standardized questionnaires (Table 3) will be administered before the start of the IACP. Many of these will be repeated after the completion of the program (Table 3). The total time required for the administration of all questionnaires will be approximately 55 to 65 minutes at baseline and 40 to 50 minutes at the end of the treatment. The total time dedicated to pre- and postintervention questionnaires may seem long but is justified by their key importance to the development of individualized treatment plans and the importance of postintervention feedback and debriefing sessions with clinical staff. All questionnaires will be administered in French, given that the language of treatment at the study site is French, and that French is the official and the most spoken language in the province where the study will be held. Language preferences will be discussed at the initial screening meeting with the clinical coordinator, and participants will have the option to request to complete the questionnaires in English at this time.

**Table 3 table3:** Psychometric properties and characteristics of the included questionnaires.

Questionnaire			Themes covered		Number of questions		Available research on validity^a^		Available research on reliability		Time necessary to complete		Time at which survey is completed (T_0_^b^; T_1_^c^)

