### Statistical Analysis

Statistical analyses will be performed using SPSS version 27.0. Feasibility and acceptability will be analyzed by summarizing quantitative data from (1) clinician-reported recruitment rate, retention rate, and adherence to protocol using descriptive statistics; (2) weekly satisfaction surveys of individual and group activities; and (3) postintervention surveys of overall satisfaction and satisfaction with the web-based mode of intervention. Qualitative data from both the weekly and overall satisfaction surveys will be analyzed using conventional content analysis. Patient characteristics at baseline will be summarized using descriptive statistics.

The preliminary effectiveness of the IACP intervention will be examined using general linear mixed models, with changes in global EDE-A scores from baseline to the end of treatment as the primary outcome. Appropriate covariates (eg, number of attended sessions) and random factors (eg, therapist) may be added to the statistical model for exploratory analysis. Similar general linear mixed model analyses will be run for the secondary outcome measures (Table 3), comparing scores from the baseline to the end of treatment. Finally, general linear mixed models will also be used to study the moderating role of the level of attendance and other clinical and psychosocial factors such as age, length of illness, ED diagnosis (anorexia nervosa vs other types of ED), and family connectedness on the primary outcome (change in EDE-A scores from baseline to end of treatment).

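### The entry rule for the effectiveness analysis can be read to require the whole questionnaire battery, so participants with both EDE-A scores could be left out because another form is missing

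*Protocol article*

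**What the plan says.** **Entry to the effectiveness analysis.** In Attrition and Compliance, participants who attend at least one session per week "and complete both pre- and postintervention materials) will be considered sufficiently exposed to the intervention and, thus, will be included in the data analysis" on preliminary effectiveness. The word *all* is absent and *materials* is not defined. The same section uses *materials* for everything the study shares with the clinical programme.

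**Adherence targets.** Table 1 (Data Collection) sets three:
- attendance alone: "At least 70% (70/100) of participants complete at least one therapeutic session per week of treatment in the IACP"
- forms alone: "At least 70% (70/100) of participants complete all pre- and postintervention questionnaires"
- both together: "At least 70% (70/100) of participants complete at least one therapeutic session per week and all pre- and postintervention questionnaires"

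**The battery.** Outcome Measures says of the baseline questionnaires: "Many of these will be repeated after the completion of the program (Table 3"). Table 3 lists 12 instruments at baseline (T0) and 10 at the end of treatment (T1). The Adolescent Coping Scale (79 items) and the internet-use questionnaire (15 items) are T0 only.

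**The analysis.** Statistical Analysis specifies general linear mixed models "with changes in global EDE-A scores from baseline to the end of treatment as the primary outcome", with similar models for the secondary outcomes. It adds no condition about completeness of other forms.

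**The concern.** The primary effectiveness outcome needs two forms, the EDE-A at T0 and at T1. If entry to that analysis depends on all 22, an observed pair of EDE-A scores is discarded when, say, a perfectionism or self-esteem form is missing. That form carries no information about exposure to treatment, which is the stated reason for the entry rule. The case is plainest for the two T0-only forms. They cannot enter a pre-post comparison, and neither is a named moderator in Objectives and Hypotheses or Statistical Analysis.

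This differs from excluding drop-outs or low attenders. Here the participant was treated and the outcome was measured. At stake are precision and, if incomplete batteries are commoner in some kinds of patient, how well the analysed group represents those treated. An entry rule open to two readings also leaves the choice to be made after the data are seen.

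**Working it through.** **1. Which reading is natural.** The entry rule has two conditions: weekly attendance and pre/post materials. Table 1's joint target has the same two, with the second written as all pre- and postintervention questionnaires. Together with the wider use of *materials* in the same section, this favours the full battery. The narrower reading, that both assessment points took place, is possible.

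**2. Size of the battery (Table 3).**
- T0: 36+6+22+13+47+7+79+20+23+15+3+6 = 277 items on 12 forms.
- T1: 277 − 79 − 15 = 183 items on 10 forms.
- Total: 12 + 10 = 22 forms, of which 2 are the EDE-A.
- The completion times in Table 3 sum to 53–65 min at T0 and 39–48 min at T1, consistent with the stated 55–65 and 40–50.
- Data Collection lists "immediately after the end of treatment (postintervention self-report and satisfaction questionnaires") at the end of treatment. If satisfaction forms count, 22 is a minimum.

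**3. The plan's sample size, as a benchmark.** A noncentral F calculation with f² = 0.15, alpha 0.05, power 0.80 and two predictors gives N = 68, matching Power Calculations before moderators and dropout are added.

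**4. Possible loss.** Retained: 100 − 25 = 75 (Table 1). For simplicity, all 75 are taken to meet the attendance condition. The documents give no per-form completion rate, so p is an assumption, and forms are taken as independent.

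If any form can be missed, 75·p²² have all forms and 75·p² have both EDE-As. If T0 is always complete, 75·p¹⁰ have all forms and 75·p have both EDE-As.

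| p | All 22 forms | Both EDE-As | Difference | All forms, only T1 can be missed | Both EDE-As, only T1 can be missed | Difference |
|---|---|---|---|---|---|---|
| 0.999 | 73.4 | 74.9 | 1.5 | 74.3 | 74.9 | 0.7 |
| 0.995 | 67.2 | 74.3 | 7.1 | 71.3 | 74.6 | 3.3 |
| 0.99 | 60.1 | 73.5 | 13.4 | 67.8 | 74.3 | 6.4 |
| 0.98 | 48.1 | 72.0 | 23.9 | 61.3 | 73.5 | 12.2 |

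Differences are taken before rounding. For example, 0.99²² = 0.8016 and 0.8016 × 75 = 60.1; 0.99² = 0.9801 and 0.9801 × 75 = 73.5.

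**5. Lower bound.** If a participant who misses one form at a visit misses them all, everyone with both EDE-As also has the whole battery, and the difference is 0.

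**The case against.** **The exclusion is not stated.** *Materials* is undefined, *all* does not appear in the entry rule, and Statistical Analysis describes outcome-by-outcome models with no completeness condition. Detailed rules for partly missing forms often sit in an analysis plan that is not shown. This stands to the extent that one cannot say such participants will be dropped. It does not remove the point, because the article itself fixes an entry rule and its likeliest reading has this effect.

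**The all-questionnaire target suits what is being piloted.** Treatment plans are built on the initial questionnaire results (Intervention). The battery's length is justified by treatment planning and feedback (Outcome Measures). Threshold scores from baseline assessments are meant to guide module selection (Future Implications). Whether the full battery can be completed is a fair feasibility question. This stands in full. A reader might infer that Table 1 should be narrowed to the EDE-A, or that one missing form makes a participant a feasibility failure. The documents support neither. Such a participant misses two of three adherence targets but still counts towards retention and the attendance target. Feasibility is summarised descriptively, with no pass/fail rule.

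**The figures lean on independence.** Forms given together at two visits, as part of care, are likely to be missed together. Table 1 also counts as recruited only those who complete the baseline measure. If that means the T0 battery, only the T1 columns apply. At 0.5% missing per form the loss is then about 3 of 75. This too stands, and the figures show sensitivity rather than a forecast.

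**Conclusion.** The concern holds for the analysis-entry rule. As written, it is most naturally read to require the whole battery, and on that reading it could discard observed EDE-A pairs because of unrelated forms.

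The size cannot be known from the documents. At an assumed 1% missing per form, independently, about 60 of 75 qualify (68 if only T1 forms can be missed), against about 74 with both EDE-As. At 2% the figures are 48 (61) against 72 (about 74 if only T1 forms can be missed). The full-battery counts at 2% fall below the plan's 68, while the EDE-A pairs stay above it. With forms always missed together the loss is nil.

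These figures rest on 75 retained, all meeting the attendance condition, and on a completion rate the documents do not give. It would go too far to say that the plan definitely excludes these participants, or that a loss of this order is expected.

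**What to change.** In Attrition and Compliance, replace the reference to pre- and postintervention materials with an outcome-specific condition, and repeat it in Statistical Analysis. A participant is not excluded from the analysis of an outcome because a different form is missing, and the EDE-A analysis depends only on EDE-A data. A moderator analysis would also need that moderator's own score, for example family connectedness. State n for each outcome.

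Keep the all-questionnaire targets in Table 1 as measures of whether the full battery can be completed. Optionally, report completion of the EDE-A at both times beside them.

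The cost is wording only. Data collection and clinical use of the forms do not change. The number analysed may differ between outcomes, and the report must show this. The change should be made before outcome data are examined.

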### Intervention

The intervention uses a family-centered, educational, and motivational approach that is based on the biopsychosocial model of EDs as described in Aimé and Bégin [46]. This model theorizes that a combination of sociocultural, environmental, familial, and individual factors, in addition to biological predispositions, converge to contribute to both the development and maintenance of disturbed beliefs and behaviors that characterize EDs. The therapeutic and psychoeducational modules (Table 2) were created based on this theory [46] and on a variety of similar sources such as books by Daniel J Siegel on mindfulness and by Martha M Linehan on impulse control [47], on cognitive behavioral and psychoeducational activities that are carried out in numerous ED treatments (eg, an open letter to my anorexia, metaphors for change, etc), and on original material created in partnership with patients.

Each participant will have an individualized treatment plan combining one or more modules, which will be established based on the initial questionnaire evaluation results and discussions between the clinician, the participant, and their family. Modules on one or more of the following themes will be presented as follows: (1) EDs and related psychopathology; (2) mental health and emotional regulation; (3) stress and anxiety management; and (4) identity, relationships, and life cycle issues in adolescence. Parents will be invited to participate in interventions pertaining to the physical and psychological components of EDs, meal accompaniment, stress, anxiety, hyperactivity management, and family life.

The intake and evaluation process, which will guide the creation of an individual treatment plan, will take place over 1 week. Following this, the intervention will take place over 4 weeks, with the possibility of extending it by 2 weeks, based on a discussion with the clinical team and the participant’s individual needs and progress. The intervention will conclude with 1 week of feedback and evaluation. Overall, the programming will last for 6 to 8 weeks.

**Table 2 table2:** Overview of the 4 therapeutic modules and corresponding activities and interventions offered within the Intensive Ambulatory Care Program.

Module	Activities and interventions
EDs^a^ and related psychopathology	Virtual meal accompaniment Hyperactivity management ED recovery and sources of motivation Perfectionism Body image
Mental health and emotion regulation	Recognizing emotions Emotion regulation Impulsivity and anger Suicidal and parasuicidal behaviors
Stress and anxiety management	Recognizing emotions Mindfulness Relaxation techniques Psychoeducation about stress
Identity, relationships, and lifecycle issues in adolescence	Changes during adolescence and fear of growing up Self-esteem and self-affirmation The influence of social media Relationships with parents and friends Communication

^a^ED: eating disorder.

The time commitment for program participants will be variable but will involve a minimum of two to three 60- to 90-minute sessions per week, including meal accompaniment and preparatory activities with the adolescent and at least one parent or guardian. This represents a total of approximately 3 to 4 hours of programing per week. This will be in addition to regular planned outpatient clinical appointments with doctors, psychologists, social workers, etc. which will be considered usual care and which are not part of the IACP.

The modules of the intervention will be delivered using various formats, including in-person and web-based individual meetings, in-person and web-based meetings with parents, web-based synchronous therapy activities (eg, relaxation or mindfulness) administered by clinicians, individual web-based asynchronous therapy activities completed alone by participants with web-based feedback provided by clinicians, web-based viewing of prerecorded informational videos, and participant and family completion of personal logbooks and assignments. Each module has a set format (eg, individual vs group; in-person vs web-based) and was developed by the clinical team based on clinical experience and relevant literature.

### Outcome Measures

A set of standardized questionnaires (Table 3) will be administered before the start of the IACP. Many of these will be repeated after the completion of the program (Table 3). The total time required for the administration of all questionnaires will be approximately 55 to 65 minutes at baseline and 40 to 50 minutes at the end of the treatment. The total time dedicated to pre- and postintervention questionnaires may seem long but is justified by their key importance to the development of individualized treatment plans and the importance of postintervention feedback and debriefing sessions with clinical staff. All questionnaires will be administered in French, given that the language of treatment at the study site is French, and that French is the official and the most spoken language in the province where the study will be held. Language preferences will be discussed at the initial screening meeting with the clinical coordinator, and participants will have the option to request to complete the questionnaires in English at this time.

**Table 3 table3:** Psychometric properties and characteristics of the included questionnaires.

Questionnaire			Themes covered		Number of questions		Available research on validity^a^		Available research on reliability		Time necessary to complete		Time at which survey is completed (T_0_^b^; T_1_^c^)
**Primary outcome (eating disorder symptoms)**													
	Eating Disorder Examination Questionnaire—Adolescent version	Eating disorder symptoms		36 items		Adolescent (11-18 years old) [48]		Good internal consistency [48]		7-8 min		T_0_, T_1_	
**Secondary outcomes (comorbidities and associated behaviors)**													
	Affective Reactivity Index	Chronic irritability		6 items		Adolescent (3-18 years old) [49,50]		Good internal consistency [49]		1-2 min		T_0_, T_1_	
	Child and Adolescent Perfectionism Scale	Trait perfectionism		22 items		Adolescents (10-17 years old) [51]		Good internal consistency [51]		3-4 min		T_0_, T_1_	
	Patient Health Questionnaire for Adolescents	Depressive symptoms and suicidality		13 items		Adolescents (grade 8-12) [52]		Good internal consistency [52]		2-3 min		T_0_, T_1_	
	Revised Children’s Anxiety and Depression Scale	Anxiety and depression		47 items		Adolescents (English version: 8-13 years old [53]; French version: 10-19 years old [54])		Good internal consistency [53]		15 min		T_0_, T_1_	
	Generalized Anxiety Disorder 7	Generalized anxiety		7 items		Adolescents (English version: 14-18 years old [55]; French version 18-75 years old [56])		Excellent internal consistency [57]Good test-retest reliability [57]		1-2 min		T_0_, T_1_	
	Adolescent Coping Scale (Échelle de coping pour adolescents)	Coping strategies		79 items		Adolescents (English version: 12-18 years old [58]; French version: 14-17 years old [59])		Good internal consistency (French version) [59]		11-13 min		T_0_	
	Self-Esteem Rating Scale, short form	Self-esteem		20 items		Adults (English version: mean 26.8, SD 9.9 years [60]; French version: mean 24, SD 7.4 years [60])		Good internal consistency (French) [60]		3-4 min		T_0_, T_1_	
	Eating Disorder Recovery Self-Efficacy Questionnaire-French	Confidence regarding eating disorder recovery		23 items		Adults (English version: mean 26.3, SD 11.1 years [61]; French version: mean 21.8, SD 3.9 years [62])		Excellent internal consistency [61] Good test-retest reliability [62]		5-6 min		T_0_, T_1_	
	Dépistage/évaluation du Besoin d’aide—internet^d^	Problematic internet usage		15 items		Adolescents (16-29 years, mean 19.7 years [63])		No data available		3-4 min		T_0_	
	Hyperactivity questionnaire (*Questions pour évaluer le surexercice*)	Excessive exercise habits		3 items		No psychometric data available^e^		No psychometric data available^e^		1-2 min		T_0_, T_1_	
	Family Connectedness Questionnaire (*Fonctionnement familial*)	Family functioning		6 items		No psychometric data available^e^		No psychometric data available^e^		1-2 min		T_0_, T_1_	
Total response time			N/A^f^		N/A		N/A		N/A		55-65 min 40-50 min		T_0_ T_1_

^a^For the purposes of this study, we consider standardized questionnaires to be validated if they have shown favorable psychometric profiles in peer-reviewed studies.

^b^T_0_: baseline

^c^T_1_: end of treatment

^d^Three additional, nonvalidated questions were added to determine problematic use of the internet to access information about (1) food and calories, (2) exercise and energy expenditure, and (3) dieting and other ways of losing weight.

^e^No psychometric data were available for questionnaires created by members of our research team. However, these questionnaires were either based on relevant literature or used in other studies. Further details are provided in Multimedia Appendix 1 [25,34,49-92].

^f^N/A: not applicable.

The primary outcome measure for this study is the Eating Disorder Examination Questionnaire for Adolescents (EDE-A) [93], a 36-item self-report questionnaire that evaluates attitudes, feelings, and behaviors related to eating, body image, and weight. It is a close adaptation of the Eating Disorder Examination Questionnaire (EDE-Q) [64], the adult version of this questionnaire, which contains 28 items and is one of the most commonly used ED symptom scales [8,94,95]. The EDE-A was adapted to measure symptoms on a shorter timescale than the EDE-Q (14 days rather than 28 days), which was considered more developmentally appropriate by experts with experience in treating EDs in the adolescent population [93] and is better suited to our study given the short length of our intervention (4-6 weeks, excluding pre- and postintervention meetings). Like the EDE-Q, the EDE-A questionnaire yields a global score in addition to four subscale scores: restraint, eating concern, weight concern, and shape concern. Norms exist for EDE-Q scores in healthy [93] and clinical adolescent populations [48].

No studies have evaluated the internal consistency of the EDE-A specifically, however, the EDE-Q, on which it is based, has good internal consistency, with a Cronbach α of .96 in a sample of female adolescents with anorexia nervosa [48], and between .78 and .93 in the general population [96,97]. Our team produced an adapted version of the questionnaire using a validated translation of the EDE-Q by Turgeon [98] as a guide, given that no validated translations of the EDE-A were available.

The secondary outcomes are outlined in Table 3 and include measures of comorbid ED psychopathology and related behaviors, including anxiety and depression symptoms, irritability, perfectionism, self-esteem, coping skills, social media use, and family connectedness. Further descriptions of the secondary outcome measures, including their psychometric properties, can be found in Multimedia Appendix 1 [25,34,49-92].

Satisfaction questionnaires (acceptability) will consist of self-report surveys completed by the participants both weekly and at the end of the intervention. Weekly surveys will evaluate satisfaction with individual therapeutic activities (eg, meal accompaniment sessions, individual and group sessions) experienced in the IACP using Likert-type questions (eg, Was this activity interesting and useful? Did it help participants understand themselves or find solutions? Did participants feel understood? Were participants satisfied and engaged?) as well as open-ended questions about what participants liked, disliked, and thought were the most important takeaways from each intervention. Postintervention satisfaction surveys for parents and patients will evaluate overall program satisfaction and satisfaction with the web-based mode of intervention, using 10-point Likert-type and open-ended questions.

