### Ethics Approval and Participant Safety

The Scientific Committee of the Sainte-Justine University Hospital Center Ethics Committee (FWA00021692), which was designated by the Quebec government (Ministère de la Santé et des Services Sociaux du Quebec) in Montreal, reviewed and approved the study protocol (project ID number: 2022-3925). Concerning the intervention itself, the risks involved are minimal and inherent to participating in therapy, such as being confronted with difficult information regarding one’s own mental health, behaviors, attitudes, etc, which can lead to stress or anxiety. However, this is a part of the treatment process and is expected to lead to positive therapeutic outcomes. The risks related to the evaluation of the intervention are minimal. There will be no inconveniences in terms of travel time and time spent responding to questionnaires other than that required for the participants’ normal follow-up in the IACP. If participants disclose worrisome information in the questionnaires, especially those related to suicidal ideation, the clinical program coordinator (a clinical psychologist) will contact them promptly to provide appropriate support. The clinical program coordinator will refer the participants to the necessary services to ensure their safety. The participants will be notified in advance that the clinical program coordinator may disclose this information to their parents or caregivers. Risks related to data and information-sharing with the research team as well as the measures in place to maintain participant confidentiality (deidentification of all data, transfer of data via a secure email account, and data storage on secure hospital servers) will also be discussed with all participants and parents during the intake meeting with the clinical coordinator.

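### Overall-program and web-delivery satisfaction is scheduled only after the intervention, so 25 to 30 of 100 enrolled participants may go unrated and the summary risks selection bias

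*Protocol article*

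**What the plan says.** Objectives and Hypotheses places acceptability beside feasibility in the primary objective. The Methods overview says what is to be acceptable: the program, and its web-based delivery.

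Data Collection sets the timing of the satisfaction questionnaires: "weekly (youth and parent satisfaction questionnaires), and immediately after the end of treatment (postintervention self-report and satisfaction questionnaires". Outcome Measures separates their content. During the program, "Weekly surveys will evaluate satisfaction with individual therapeutic activities". At the end, "Postintervention satisfaction surveys for parents and patients will evaluate overall program satisfaction and satisfaction with the web-based mode of intervention", on a 10-point scale with open questions. Statistical Analysis uses both sources for acceptability, listing "weekly satisfaction surveys of individual and group activities" next to the postintervention surveys.

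On losses, Attrition and Compliance states: "we expect attrition to be less than or equal to 25% (25/100"). It cites dropout of 7% to 42% in comparable programs. Table 1 sets a target of at least 70 of 100 completing all pre- and postintervention questionnaires.

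On collection, "The clinical program coordinator will be responsible for collecting all data, deidentifying the data, and sending all deidentified data" to the research team. Ethics Approval and Participant Safety identifies the coordinator as a clinical psychologist.

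On format, the Intervention section says: "Each module has a set format (eg, individual vs group; in-person vs web-based"). Strengths and Limitations looks to the satisfaction data for clues about the in-person and web-based components. Its list of limitations mentions neither selective response nor courtesy bias.

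**The concern.** The two ratings that match the plan's own definition of acceptability are taken at one time point, after treatment. A family that stops in week two or three may never reach it. If dissatisfaction or burden is among the reasons for stopping, the people left to answer are a favourable selection.

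At stake is half of the primary objective. The Discussion says that a feasible, acceptable and preliminarily effective program could readily be applied elsewhere. A mean satisfaction score from completers, read as the view of all enrolled families, would feed into that conclusion.

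A smaller worry points the same way. Answers pass through the program's own clinical coordinator before deidentification, so deidentification shields respondents from the research team but not from the program.

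**Working it through.** **Inputs from the protocol article**
- Enrolled: 100 (Power Calculations).
- Attrition: at most 25% (Attrition and Compliance).
- Questionnaire completion: at least 70% (Table 1).
- Cited dropout range: 7% to 42% (Attrition and Compliance).
- Rating scale: 10 points (Outcome Measures).

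**Inputs assumed.** The article gives no satisfaction scores. The completer-leaver gap is varied from -1 to 4 points. For the bounds, the completer mean is taken as 8 on a scale running from 1 to 10.

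**Step 1: the plan's own figure.** 100 × (1 - 0.25) = 75 retained, so 25 leave. This agrees with the stated 25/100 and with the 75/100 retention in the abstract.

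**Step 2: how many may have no overall or web-delivery rating.**
- At the attrition limit: 25 of 100.
- At the completion target: 100 - 70 = 30 of 100. This is an allowance, since someone may miss another questionnaire and still answer this one.
- Over the cited dropout range: 7 to 42 of 100.

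**Step 3: bias of a completer-only mean.** Let d be the share missing, C the completers' mean and L the leavers' mean. The all-enrolled mean is (1 - d)C + dL. The completer mean therefore overstates it by C - [(1 - d)C + dL] = d(C - L).

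| Share missing d | Gap -1 | Gap 0 | Gap 1 | Gap 2 | Gap 3 | Gap 4 |
|---|---|---|---|---|---|---|
| 7% | -0.07 | 0 | 0.07 | 0.14 | 0.21 | 0.28 |
| 25% | -0.25 | 0 | 0.25 | 0.50 | 0.75 | 1.00 |
| 30% | -0.30 | 0 | 0.30 | 0.60 | 0.90 | 1.20 |
| 42% | -0.42 | 0 | 0.42 | 0.84 | 1.26 | 1.68 |

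If only half of a 25% loss rates lower and the other half rates like completers, a 2 to 3 point gap gives 0.25 × 0.5 × 2 = 0.25 to 0.25 × 0.5 × 3 = 0.375.

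**Step 4: what completer data alone can bound.** With C = 8, set every missing rating to 1 and then to 10.
- d = 25%: 0.75 × 8 + 0.25 × 1 = 6.25, up to 0.75 × 8 + 0.25 × 10 = 8.50.
- d = 42%: 0.58 × 8 + 0.42 × 1 = 5.06, up to 0.58 × 8 + 0.42 × 10 = 8.84.

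**Step 5: whether the weekly surveys close the gap.** They rate single activities and stop at departure. They show what leavers thought of the sessions they attended, but they do not give those leavers' rating of the program as a whole or of web delivery.

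**The case against.** Several stronger readings are tempting, and the article does not support them.

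- *Leavers never answer.* The article does not say so. It does not say what happens when treatment ends early, and an article may leave exit procedure to the full protocol. Leavers also contribute weekly ratings and open comments until departure, and these count as acceptability data. What remains is that the stated timing is postintervention and no early-exit administration is described.
- *The ratings are biased upward.* This is plausible but not established. The Population section provides for discontinuation on medical or acute psychiatric grounds, which need not reflect dissatisfaction. A zero gap gives no bias, and a negative gap reverses it.
- *There is no in-person rating to set against the web rating.* This is wrong. Weekly surveys rate activities, and each module has a set format, so in-person activities are rated. They only need to be tabulated that way.
- *Surveys should go straight to the research assistant.* This conflicts with the plan's data flow, in which the research team receives only deidentified data, a safeguard explained to families. The article also does not say that the coordinator delivers the therapy being rated, so a courtesy effect is possible but cannot be sized.

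Two further points for the plan are fair. Retention is reported as a feasibility outcome, so completer ratings would not be read in isolation. Table 1 sets no acceptability threshold, so no stated decision rule turns on a shift of half a point. These limit the consequence of the problem. They do not supply the missing ratings or tell the reader how many families stand behind the mean.

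**Conclusion.** The point holds as a risk of selection bias in part of the primary objective. Followed as written, the plan yields a largely completer-based summary of overall-program and web-delivery satisfaction, with up to 25 to 30 of 100 enrolled participants possibly unrepresented. At 25% missing, an assumed gap of 0 to 4 points moves the mean by 0 to 1.0 points. These sizes rest on assumed gaps and on leavers giving no overall rating. Upward is the plausible direction where leaving reflects dissatisfaction or burden, but the documents fix neither sign nor size. Courtesy bias through collection by the coordinator is a secondary, unquantified caveat.

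**What to change.** 1. Offer the existing overall satisfaction survey to participant and parent whenever they leave the program, including early stops, through the current collection route.
2. Report the overall and web-delivery results with the number responding out of all enrolled, and show leavers' last weekly ratings beside them.
3. Tabulate weekly activity ratings by the set format of each activity, in-person or web-based. This supplies the clues that Strengths and Limitations expects from the satisfaction data.
4. State as a limitation that the clinical program coordinator collects the answers, so some courtesy bias is possible.

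The cost is one short extra survey contact at exit, an extra tabulation and a sentence in the limitations. Some leavers will not respond, so the selection problem is reduced and made visible but not removed.
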